## Methods

### Participants and procedure

Six secondary schools in the East of Flanders are contacted to participate in the study. Participants are adolescents in their first year of secondary school (7th grade, ages 11–13). The aim is to reach 300 students spread over 16 classes. We ensure the inclusion of students from different Socio Economic Status (SES) groups and various educational levels to compose a heterogeneous sample. In Belgium, there are two educational levels in secondary school. The first education level, grade A, is considered as a broad first grade in which students receive basic knowledge on technics, mathematics, or languages, with the intention to prepare them on a more specific educational program in the second grade. The second education level, grade B, is intended for students with specific needs. Both are included.

Schools that are interested are asked to participate with as many first-grade class groups as possible. If they give their consent to take part in the study, they are randomized by the researcher in a intervention or a control group. Finally, six rural schools with comparable background and meeting the same language criteria decided to participate in the study. All schools receive information letters for students and their parents, which contain detailed information about the study aims and procedure. Parents can either give or withhold their permission for including their child’s data in the study, and both parents and children are free to withdraw from the study at all times. The Boost Camp program is incorporated in the class curriculum, so all participants in the intervention condition receive the program. The advantage of incorporating the program in the class curriculum is that all adolescents participate and interact. To ensure that the intervention and the control schools place an equal emphasis on students’ mental health, teachers of all participating schools receive a workshop on care management and are invited to sign a school charter on the importance of emotional well-being of the schoolchildren.

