### Data analysis

Power analyses were calculated to determine the required sample size for detecting a clinically significant difference between the intervention and control group at 6 months follow-up on one primary outcome (FEEL-KJ). With a significance level of α = 0.05 and a power level of β = 0.90, a total sample of 86 N_Non-cluster_ participants is needed to detect a significant difference. However, the clustering of participants within schools has to be considered and therefore, the design effect is calculated as 1 + (m-1)*ICC, with m referring to the number of participants per cluster [57]. Based on prior research determining the ICC values for adolescent health outcomes [121], an Intraclass Correlation Coefficient (ICC) of 0.02 was used. The estimated average size of the classes participating in current study is counted on 20 students per class, resulting in a design effect of 1,38. Moreover, as the intervention requires a high time investment, an 3:2 ratio in favor of the control group will be chosen at randomization. Following the recommendations of Gao et al. [57], the final calculation of the total sample of the control group was multiplied by the design effect with the randomization ratio and the N_Non-Cluster,_ resulting in a total sample size of 241 students, 145 for the control group and 97 for the intervention group. Taking into account declined participation and loss to follow-up, a drop-out rate of 20% is estimated. Finally, this resulted in a required sample size of 291 students, 174 in the control group and 117 in the intervention group, clustered in at least 16 classes.

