Assumptions will be checked by examining descriptive statistics and missing variables will be examined. When data are missing completely at random, maximum likelihood estimation will be used to estimate the missing values. When data are not missing completely at random, generalized estimating equation analyses will be used. Possible baseline differences in both groups will be assessed using simple t-tests or chi-square tests, and variables that show baseline differences will be entered as covariates of no interest in all models. To assess the difference between the intervention and control condition in the change in the use of adaptive ER skills and in emotional wellbeing during 6 months following the program, a mixed model will be used. More specifically, a mixed model with fixed effects for condition (intervention or control), time (immediately after intervention, 2 months post FU, and 6 months post FU), and their interaction, adjusted for baseline will be used. Moderators will be added one by one. To account for the nested structure of students within classes, and classes within schools, a random intercept for schools and a random intercept for classes nested within schools will be utilized. To account for the temporal correlation of measurements within a student, an unstructured residual covariance will be assumed.

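### The missing-data rule is the wrong way round: it leaves likelihood for GEE when data are not MCAR, which is where likelihood has the advantage

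*Protocol article*

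**What the plan says.** The Data analysis section gives a rule with two branches. The first is: "When data are missing completely at random, maximum likelihood estimation will be used to estimate the missing values". The second is: "When data are not missing completely at random, generalized estimating equation analyses will be used". For the second branch it mentions no weighting, imputation or working correlation.

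The same paragraph then names the effectiveness analysis: "a mixed model with fixed effects for condition (intervention or control), time" and their interaction, adjusted for baseline. For clustering, "a random intercept for schools and a random intercept for classes nested within schools will be utilized". For repeated measures within a student, "an unstructured residual covariance will be assumed". It does not say how this model relates to the GEE branch.

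The sample size paragraph of that section states that "a drop-out rate of 20% is estimated". That figure covers declined participation as well as loss to follow-up.

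**The concern.** Ordinary GEE and likelihood rest on different missing-data assumptions, and GEE's is the stronger. The rule reserves likelihood for the case where the choice makes no difference and gives it up where it could help.

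The outcomes are repeated self-reports of mood and emotion regulation, and the Strengths and limitations section says participants are not blind to allocation. Dropout that depends on earlier scores, and does so differently by arm, is therefore plausible, though nothing in the article establishes it. If it occurred, the rule could move the main comparison from an approximately unbiased estimator to one without that protection.

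The rule also lets a judgement about MCAR pick the estimator. Observed data can refute MCAR. They cannot confirm it, nor tell MAR from MNAR.

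**Working it through.** The article gives no figure to reproduce on this point. The check is a comparison of assumptions, followed by simulation to size the effect.

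**1. Validity by mechanism**

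| Missingness | Likelihood mixed model | GEE, no weighting or imputation | Branch chosen by the rule |
|---|---|---|---|
| MCAR | valid | valid | likelihood |
| Depends only on covariates in the model | valid | valid | GEE |
| MAR through earlier outcomes | valid if the model is correct | not guaranteed | GEE |
| MNAR | not valid | not valid | GEE |

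In no row does moving to GEE gain anything. In the third row it can lose.

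**2. Size under a null effect.** Assumptions, not taken from the article: true effect 0, correlation 0.6 between times, about 20% missing at T3, dropout driven by the T1 score with logit slope 0.8. School and class clustering was not part of the bias check.

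- Score-dependent dropout in one arm only: working-independence GEE biased by 0.037 and 0.048 SD in two runs; exchangeable GEE 0.012.
- Opposite slopes by arm: independence 0.074 and 0.067 SD in absolute size; exchangeable 0.006.
- Same slope in both arms: independence -0.008; exchangeable -0.012.
- Likelihood: 0.00.

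Monte Carlo error was about 0.01 for the exchangeable and same-slope results.

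**3. Size under a real effect.** Assumptions: true effect 0.30 SD, n = 300, 3:2 allocation (the article has "an 3:2 ratio in favor of the control group will be chosen at randomization"), three follow-up visits, unequal correlations of 0.3 to 0.7, dropout driven by the previous score with slope 0 or ±1, 16% to 23% missing at the last visit. Means of 200 runs, Monte Carlo SE about 0.01:

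| Dropout mechanism | Likelihood | GEE, independence | GEE, exchangeable |
|---|---|---|---|
| MCAR | 0.316 | 0.313 | 0.316 |
| MAR, same in both arms | 0.304 | 0.288 | 0.302 |
| MAR, control arm only | 0.303 | 0.217 | 0.303 |
| MAR, opposite by arm | 0.315 | 0.122 | 0.311 |
| MAR, opposite, signs reversed | 0.284 | 0.446 | 0.288 |

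With working independence and dropout that differs by arm, the bias runs from 0.122 - 0.30 = -0.18 to 0.446 - 0.30 = +0.15. These slopes are steeper than in step 2. Likelihood and exchangeable GEE stay within 0.02 of the truth throughout.

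**4. The powered outcome.** Table 1 shows that FEEL-KJ is not measured at T1, so its own scores can drive dropout only through T0 or T2. With baseline in the model, T0-driven dropout left independence GEE with a bias of 0.002. T2-driven dropout gave 0.04 to 0.07 with independence, and 0.004 and -0.003 with exchangeable.

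**5. Scale.** The stated 86 participants at alpha 0.05 and 90% power imply a detectable difference of about 0.7 SD (two-sided comparison of two means, equal groups assumed). A bias of 0.04 to 0.07 is 0.04/0.7 = 6% to 0.07/0.7 = 10% of that.

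**6. Six schools, a separate matter.** Under Participants and procedure, "six rural schools with comparable background and meeting the same language criteria decided to participate in the study". Assume a 3 versus 3 split and a school-clustered sandwich z-test with no correction. Its variance divides by 3 per arm where an unbiased one divides by 2, so it is too small by a factor of 2/3. The test rejects when |t| on 4 df exceeds 1.96 × √(2/3) = 1.60, which has probability 18.5%. Simulation gave 17% to 19% at ICC 0 to 0.05. This occurs with no missing data at all.

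**The case against.** The strongest reply is that the harm depends on details the article does not fix. Working correlation, weighting and standard-error correction are commonly left to an analysis plan, and the companion model's unstructured covariance makes working independence a doubtful default. With an exchangeable working correlation, GEE tracked likelihood closely in every scenario above, even where the true correlations were unequal. This stands, and it limits what can be said about size. It does not rescue the rule, because the assignment of methods to conditions is stated outright and no choice of working correlation makes GEE the better method when data are not MCAR.

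Three stronger readings are tempting and are not supported.

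- A reader might infer that GEE is invalid, or biased, whenever data are not MCAR. It is not guaranteed valid. Missingness that depends only on modelled covariates leaves it valid, and visible bias in these simulations needed both working independence and dropout that differs by arm.
- A reader might infer that the rule inflates the type I error to about 18%. That figure comes from an uncorrected test on six clusters, arises with complete data, and assumes a GEE specification the article does not state. Few clusters also threaten uncorrected tests in the mixed model.
- A reader might infer that GEE certainly replaces the mixed model. The article does not say how the two relate. Replacement is one reading, and the text should settle it.

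**Conclusion.** The point holds as an error in what is written: the two methods are attached to the wrong conditions, and an MCAR check cannot support the choice in any case. The conclusion about direction rests on standard missing-data theory and on reading GEE as plain GEE, since no weighting or imputation is mentioned.

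The size is conditional. A bias of about 0.04 to 0.07 SD needs working independence, about 20% dropout, and score-dependent dropout that differs by arm, under the assumed slope of 0.8 and correlation of 0.6. Steeper assumed slopes gave more, and a suitable working correlation or a common dropout mechanism gave close to none. Because the stated 20% includes declined participation, loss after baseline may be smaller. Nothing in the article shows that the adverse case will arise. The correction is worth making because it is cheap and the present rule has no compensating benefit.

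**What to change.** Delete the MCAR-based switch. State that the baseline-adjusted likelihood mixed model already described, with its school and class random intercepts and unstructured residual covariance, will be fitted to all observed follow-up data as the primary analysis whatever an MCAR check shows. Add one sensitivity analysis for departures from MAR, for example a delta shift applied to unobserved outcomes. If GEE is kept, make it a sensitivity analysis with inverse-probability weights.

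As a separate line, name a small-sample correction suited to six randomised schools for whichever method supplies the inference.

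The cost is two rewritten sentences, one added sentence on the correction and one sensitivity run. No design change or extra data collection is needed.

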### Design

The effectiveness of Boost Camp will be tested by a clustered randomized controlled trial (cRCT) with two conditions, e.g. an intervention and a control condition (see Fig. 1). Randomization is clustered by school, which reduces the risk of contamination.

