However, some limitations of the present study can be identified as well. First of all, the randomization at school-level increases the risk of different participants characteristics, like social economic status, which in turn decreases the chance to create a perfectly matched and equivalent control group and increases the risk of selection bias [80]. Furthermore, there is no active control group used, because up until now, there is no other existing Dutch school-based ER prevention program to which Boost Camp could be compared. Second, emotional wellbeing is only assessed by self-report measures which includes possible response biases through social desirability or a lack of introspection [6]. Finally, participants and trainers were not blind to the allocated intervention, through which it is possible that adolescents in the intervention condition try harder to be aware and effective regulating their emotions, which is known as the Hawthorne Effect [80]. However, educational research trials often lack blinding as a design feature due to the high visibility of the interventions. Moreover, other evaluation methods cannot improve this because they also will not operate blinding [80].

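### The additional covariates for every model are chosen by baseline t-tests and chi-square tests that ignore school randomisation and do not measure prognostic value

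*Protocol article*

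**What the plan says.** The Data analysis section gives a two-step rule. First, "Possible baseline differences in both groups will be assessed using simple t-tests or chi-square tests". Second, "variables that show baseline differences will be entered as covariates of no interest in all models". It names no candidate variables and no threshold.

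The same section fixes the rest of the outcome model: condition, time "and their interaction, adjusted for baseline will be used", with "a random intercept for schools and a random intercept for classes nested within schools will be utilized" and an unstructured residual covariance within student.

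The Design section states that "Randomization is clustered by school, which reduces the risk of contamination". Participants and procedure reports that "six rural schools with comparable background and meeting the same language criteria decided to participate in the study" and that "The aim is to reach 300 students spread over 16 classes". Strengths and limitations concedes that "the randomization at school-level increases the risk of different participants characteristics, like social economic status".

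**The concern.** Two things are wrong with the rule as written.

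- **The tests do not match the design.** The outcome model has school and class intercepts, and the sample-size paragraph acknowledges that clustering within schools matters. The tests that choose the model's covariates have no such terms and treat students as if allocated one by one.
- **The criterion is the wrong one.** A baseline p-value measures imbalance between arms. Adjustment gains precision from variables that predict the outcome. The rule can admit a weak predictor that happens to differ and leave out a strong one that happens not to. A cluster-adjusted test would cure the first fault but not this one.

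At stake is whether the adjusted treatment estimate is defined before the data are seen. Flagged variables go into every model, so one chance flag changes all primary, secondary and moderator analyses. Gender, parent-rated problems and executive functioning are planned moderators, yet each could also enter or stay out of the main-effect models on the strength of a baseline test.

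**Working it through.** **Inputs from the article.** Six schools and a target of 300 students (Participants and procedure); ICC 0.02, class size 20 and design effect 1.38 (Data analysis).

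**Assumptions.** The baseline tests use a two-sided 0.05 threshold (none is stated). The ICC of 0.02 holds at school level and for the baseline variables; the article takes it from research on adolescent health outcomes and gives no ICC for variables such as gender or parent ratings.

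**1. The article's own design effect.** DE = 1 + (m − 1) × ICC = 1 + 19 × 0.02 = 1.38. This reproduces.

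**2. Design effect at the randomised unit.** 300 / 6 = 50 students per school, so DE = 1 + 49 × 0.02 = 1.98.

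**3. How often a simple test flags a variable with no true difference.** Rate = 2 × [1 − Φ(1.96 / √DE)].

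| Setting | DE | Flag rate | Multiple of 5% |
|---|---|---|---|
| Class level, m = 20, ICC 0.02 | 1.38 | 9.5% | 1.9 |
| School level, m = 50, ICC 0.01 | 1.49 | 10.8% | 2.2 |
| School level, m = 50, ICC 0.02 | 1.98 | 16.4% | 3.3 |
| School level, m = 50, ICC 0.05 | 3.45 | 29.1% | 5.8 |

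With the article's smaller total of 241 students (about 40 per school) and ICC 0.02, the rate is 14.2%. Simulation of the ordinary t-test (50 per school, ICC 0.02, 40,000 replicates) gave 16.7% with three schools per arm and 16.2% with four against two, so the split of schools hardly matters.

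**4. Number of chance flags.** Table 1 marks 15 measures at T0. If all were candidates, which the article does not say, the expected number of chance flags would be 15 × 0.164 = 2.5, against 15 × 0.05 = 0.75 for tests that hold their level.

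**5. Does the excess reach the treatment test?** A simulation with no treatment effect used six schools of 50, ICC 0.02, five covariates jointly explaining 16% of outcome variance (0.4²), selection by the simple t-test, and a comparison of adjusted school means (4,000 replicates). The type I error was 4.7% after selection and 5.1% with all covariates fixed in advance. The Monte Carlo standard error is √(0.05 × 0.95 / 4000) = 0.3 percentage points. Further simulations of this kind, with 5 or 14 covariates, gave 3.7% to 5.1% after selection.

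**6. Precision.** With strong predictors, the SD of the treatment estimate was 0.178 under selection against 0.163 with the predictors fixed in advance (0.178 / 0.163 = 1.09). A second set gave 0.184 against 0.167 (ratio 1.10). The loss is therefore about 9% to 10% in SD in that favourable case. Compared with adjusting for baseline alone, selection was no worse (for example 0.170 against 0.173).

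These simulations used a school-level test, not the mixed model in the article. They show what selection does, not how that model performs with six schools.

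**The case against.** The strongest defence is that the rule does little damage. The most useful covariate, the baseline value, is adjusted for whatever the tests show. A flagged variable is a real imbalance in this sample even if it arose by chance, and with six schools such imbalance is a risk the article itself names. Adjusting for it is a sensible instinct, and in simulation selection neither raised the type I error nor did worse than baseline adjustment alone. The size of the over-rejection also depends on assumptions: on the article's class-level figures it is about twofold, not threefold.

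Most of this stands, and it rules out two stronger readings that a reader might infer.

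- **That the intervention's false-positive rate is inflated threefold, or at all.** The excess applies to the baseline tests. Nothing in the article or the simulations carries it over to the treatment test.
- **That the whole primary model is data-driven.** The article fixes condition, time, their interaction, baseline adjustment, both random intercepts and the residual covariance. Only the additional covariates are left to the data.

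The defence does not rescue the selection criterion. Expecting imbalance between schools is a reason to name likely prognostic variables beforehand, not to let an invalid test choose them afterwards. Nor is this a detail left to an analysis plan: the rule is stated in full.

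**Conclusion.** The point holds as a flawed covariate-selection step with a modest consequence. At the article's ICC and about 50 students per school, the screening tests flag chance differences about 16% of the time. The plausible range runs from 9.5% (class-level design effect) to 29% (school ICC 0.05), given a two-sided 0.05 threshold. The treatment test keeps a type I error near or slightly below 5% in simulation. What is lost is a fixed definition of the adjusted estimate and, where strong predictors go unselected, some precision. That the rule is written and unsuited to the design is certain; the exact over-rejection is not, because the threshold, the school-level ICC of the baseline variables and the candidate list are not given.

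**What to change.** Delete the baseline significance tests and the sentence that makes covariates depend on them. In their place:

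- Name one small adjustment set for every model, chosen on prognostic grounds: the baseline value of the outcome (already planned), gender, and educational level (grade A or B). Add SES if it is collected, since the article names it as a likely imbalance; the article does not list a measure of it.
- Keep covariates that vary only between schools few. Six schools in two arms leave 6 − 2 = 4 degrees of freedom at school level, and educational level would draw on these if it is constant within schools.
- Report baseline characteristics descriptively, by arm and by school, without p-values.
- Treat a notable imbalance in a variable not on the list in a sensitivity analysis labelled as such.

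The cost is a sentence or two of analysis text and no new data, provided SES is added only if already collected. The downside is that a chance imbalance in an unlisted variable would not alter the primary estimate and would be addressed only in the sensitivity analysis.

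### With six randomised schools, the GEE fallback with its ordinary sandwich variance would test the condition contrast at about 18.5% instead of 5%; the planned mixed model is affected far less

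*Protocol article*

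**What the plan says.** The Design section sets the unit of allocation: "Randomization is clustered by school, which reduces the risk of contamination". Participants and procedure gives the number of units: "six rural schools with comparable background and meeting the same language criteria decided to participate in the study". The same section gives the scale: "The aim is to reach 300 students spread over 16 classes".

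The Data analysis section fixes two analyses. The main one is a mixed model with condition, time and their interaction, adjusted for baseline, with unstructured residual covariance within student, and "a random intercept for schools and a random intercept for classes nested within schools will be utilized". The other applies to incomplete data: "When data are not missing completely at random, generalized estimating equation analyses will be used". For GEE the section gives no clustering level, working correlation, variance correction or reference distribution. For the mixed model it gives no degrees-of-freedom method, and it prescribes no large-sample test either.

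The sample size in the same section is set for the 6-month contrast on the FEEL-KJ: "With a significance level of α = 0.05 and a power level of β = 0.90", and "an Intraclass Correlation Coefficient (ICC) of 0.02 was used". The design effect is computed with 20 students per class.

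**The concern.** Condition varies only between schools. Six school means, less one mean per arm, leave 4 degrees of freedom for the between-arm contrast at a given wave, however many students are measured.

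The GEE sandwich variance is justified by a large number of independent clusters. With six, it is biased downwards and very variable, and a normal reference ignores both faults. The fallback is not remote: the protocol expects 20% drop-out, and missing completely at random is the strictest missing-data condition, so any judged departure from it moves the analysis to GEE.

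At stake are the p-values and confidence intervals for the condition contrast at each wave, above all the 6-month contrast on which the trial is powered. A claim that the programme works could rest on a test whose real level is more than three times the nominal one.

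**Working it through.** **Inputs.** From the protocol: 6 schools, 16 classes, α = 0.05 (two-sided assumed), power 0.90, ICC 0.02, 20 students per class, 3:2 allocation in favour of control, 241 students before the drop-out allowance. Assumed because not stated: d = 0.5, and how the 0.02 divides between school and class. The Abstract gives 150 per arm and Data analysis gives 3:2, so school splits of 3 v 3 and 4 v 2 were both considered.

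**1. The plan's own figure.** Design effect = 1 + (20 − 1) × 0.02 = 1.38. With d = 0.5, ((1.960 + 1.282)/0.5)² = 42.03.
- Intervention: (1 + 1/1.5) × 42.03 = 70.05; × 1.38 = 96.7.
- Control: 1.5 × 70.05 = 105.07; × 1.38 = 145.0.
- Total: 241.7, against the stated 241 (145 + 97).

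The figure reproduces if the printed 86 is a per-arm number. It allows for clustering at class size and makes no allowance for six randomised units.

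**2. GEE, ordinary sandwich, clustered on school, 3 v 3 equal schools.** Within each arm the sandwich divides the squared deviations of the school means by k where the unbiased estimate divides by k − 1. With k = 3 its variance is (k − 1)/k = 2/3 of the unbiased one. The robust z therefore equals the school-mean t statistic divided by √(2/3), and it exceeds 1.96 when |t₄| > 1.96 × √(2/3) = 1.600.
- Type I error = P(|t₄| > 1.600) = 0.185. The ICC does not enter.
- Coverage of a nominal 95% interval = 1 − 0.185 = 81.5%.
- Interval length relative to a correct one on 4 df = 1.600/2.776 = 0.58.

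**3. Simulation under the null.** 6 schools, 16 classes, 15 analysed students per class, one time point, splits 3 v 3 and 4 v 2, 1,500 runs per scenario (Monte Carlo error about 0.6 to 1.1 points). Rejection at nominal 5% for the mixed model with school and class intercepts:

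| Where the 0.02 lies | REML Wald z | ML Wald z |
|---|---|---|
| All at school | 7.3-9.5% | 9.4-13.4% |
| Half school, half class | 5.1-6.5% | 6.6-8.5% |
| All at class | 3.7-4.8% | 5.1-6.1% |

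School-clustered GEE z rejected in 18.7-22.5% of runs with all 0.02 at school, and in 17.2-24.7% over all scenarios (school ICC 0 to 0.05, class ICC 0 to 0.02). With all 0.02 at school:
- GEE clustered on class: 16.2-17.7%.
- School-clustered GEE with t on 4 df but an uncorrected variance: 9.6-11.8%, so both corrections are needed.
- REML with t on 4 df imposed: 1.6-2.3%, conservative.
- t-test on six school means, 4 df: 4.1-5.6%.

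A balanced one-way check with 400,000 trials gave 7.8% (40 students per school) and 8.5% (50) for the REML-type Wald z at school ICC 0.02, and 5.0% for the school-mean t-test.

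**4. Power on 4 df.** With 241/6 = 40.2 students per school, 3 v 3, ICC 0.02 at school and d = 0.5: variance of the contrast = (0.02 + 0.98/40.2) × 2/3 = 0.0296, noncentrality = 0.5/√0.0296 = 2.91, and power against the critical value 2.776 is about 59%.

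**The case against.** The best defence is that the protocol names models and leaves inference details to an analysis plan that is not shown. It prescribes no Wald z test, no 1.96 cut-off and no uncorrected sandwich. Kenward-Roger is an option within the mixed model already planned. For the mixed model this defence largely stands. The level also depends on where the ICC of 0.02 sits, which the protocol leaves open: it speaks of clustering within schools but applies the value to class size.

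Three stronger readings are tempting and are not supported.
- A reader might infer that the 5% level fails for the mixed model. It need not: no large-sample test is prescribed, and even with one under REML the level runs from about 4% to about 8-9% at ICC 0.02.
- A reader might infer that every test at every wave is affected. The model has random intercepts only, so the condition-by-time interaction rests mainly on within-student information. The 4-df argument belongs to the condition contrast at a wave.
- A reader might infer that 2.776 is the correct critical value throughout. Imposed on the REML fit it rejects only about 2%. It is exact for the school-mean t-test.

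The defence does not clear the GEE fallback. Choosing GEE for six clusters is a stated commitment, its ordinary variance fails badly here, and a t reference alone does not repair it. The 18.5% does remain conditional on the variance being left uncorrected.

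**Conclusion.** The point holds for the fallback and, in weaker form, for the mixed model. GEE with its ordinary sandwich variance would test the condition contrast at about 18.5% (3 v 3 equal schools, any ICC), or 17-25% across the scenarios examined, so its p-values and intervals would be wrong. The mixed model with a REML Wald test would run at about 8% if the 0.02 is all at school level, 5-7% if about half is, and near nominal if it is at class level. That test is not prescribed, so this part is a request to name the method and not an error in the plan.

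The simulations assume normal data, equal class sizes, one time point, no baseline adjustment and an independence working correlation. Kenward-Roger and Satterthwaite were not run; t on 4 df stood in for them. The 59% power rests on d = 0.5, inferred from the stated sample size, and on the whole ICC lying at school level.

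**What to change.** - **Missing data.** Replace the GEE fallback by the likelihood-based mixed model, which remains valid when data are missing at random; ordinary unweighted GEE does not have that property in general. If GEE is kept, cluster on school, use a bias-corrected sandwich variance, and refer the statistic to t on 4 df.
- **Mixed model.** State REML with Kenward-Roger or Satterthwaite degrees of freedom for the condition contrast at each wave. Add a t-test on the six baseline-adjusted school means (4 df) as a check.
- **Not a remedy.** A school-level permutation test cannot reach 0.05: the smallest two-sided p is 2/20 = 0.10 for 3 v 3 and 1/15 = 0.067 for 4 v 2.

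The cost is a few sentences and no new data. The price is wider intervals and less power than the stated 90%: about 59% on the 4-df school-level test under the assumptions above. The plan should say so, and say at which level the ICC of 0.02 is meant to apply.
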